### Recruitment

All children in the 4 to 9-year age group who report to the Paediatric Dentistry Departments of Christian Dental College with symptoms typical of irreversible pulpitis in their primary molars will be considered for recruitment. Participant recruitment will be based on the defined inclusion and exclusion criteria. Recruitment is planned to start in February 2024 and expected to last for up to 8–10 months. No financial or non-financial incentives will be provided to trial investigators or participants for enrolment. A trial schematic outlining the screening, recruitment, randomisation, allocation, follow-up time-points, and planned data analysis is shown in Fig. 2.

**Fig. 2 Fig2:**
[figure not shown]
Trial schematic of the proposed study

### Randomisation and sequence generation

The randomization list will be generated before participant enrolment. Permuted block randomisation will be used to randomly assign one of the two treatment interventions to consenting trial participants who meet all the inclusion/exclusion criteria. Block lengths will vary according to a sequence generated by an external researcher. The on-site trial investigators will be blinded to the block sizes and the randomization sequence.

### Allocation concealment

The generated randomization sequence will be distributed in sequentially numbered opaque sealed envelopes (SNOSE). An independent allocator, not involved in the assessment and recruitment of the patient, will open the sequentially numbered envelope, and inform the clinical investigator which treatment group the patient is assigned to. Patient details will be written on the outside of the envelopes (that contain carbon paper overlying the treatment allocation paper), so that patient names are transferred to the allocation paper before the envelope is opened and can be audited at the end of the trial.

### Blinding

Blinding of trial participants or clinical investigators will not be possible due to evident differences between the two trial interventions. However, post-operative clinical outcomes will be assessed by an experienced paediatric dentist who is blinded to the treatment allocation, while the radiographic outcomes will be independently assessed by two different paediatric dentists. An external researcher, not directly involved in the clinical part of the study, will generate the randomization sequence, provide the SNOSE for treatment group allocation, and perform the statistical analysis of the de-identified data.

### Data collection, management, and confidentiality

Relevant demographic, clinical, radiographic, and pain intensity data will be collected at baseline and subsequently at the follow-up time points described earlier. All data collected will be recorded electronically at the trial site using unambiguous, standardized terminology and abbreviations to avoid misinterpretation. Checks will be applied at the time of data entry before data is committed to the electronic database to ensure accuracy of entered trial data. Any later modifications to data entered in the database will be documented. All participant data will be de-identified and stored on an institutional password protected computer. Data will only be accessible to authorized members of the research team. Data will be treated confidentially and stored for 3 years before being destroyed.

### Statistical methods

All analyses will use the ‘intention to treat’ principle. Baseline demographic and clinical data will be summarised for each treatment group. Binary logistic regression models will be applied to analyse all outcome measures stated in the protocol adjusting for covariates thought to be of prognostic importance. Appropriate parametric or non-parametric tests will be used to determine any significant relationship between treatment outcomes and variables in the study (age, gender, tooth/caries type, and pre-operative furcal rarefaction/pain intensity). For all statistical tests, we will use 2-sided *p*-values with α ≤ 0.05 and the treatment effect estimates will be presented with 95% confidence intervals. Up-to-date versions of SPSS (Chicago, IL, USA) will be used to conduct the statistical analysis.

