## Methods

### Trial design

This clinical study is a parallel, two-armed, open label, non-inferiority randomised controlled trial with a 1:1 allocation ratio between the experimental intervention arm (pulpotomy) and the active comparator arm (pulpectomy).

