Standard clinical protocol for the pulpotomy group:Detailed history of symptoms will be verified and a thorough clinical examination shall be performed.Pre-operative pain intensity will be recorded using the validated five-face visual analogue scale (VAS) commonly used for pain intensity measurement in children (Fig. 1). After giving explanations of the VAS, children will be requested to select one of the faces that best reflect their pain intensity.A standard pre-operative periapical radiograph will be taken using a paralleling technique and a film holder device. Care will be taken to ensure that the radiographic image extends beyond the root tip of the primary molar tooth and there is no evidence of distortion, overlap, or processing errors.Local anaesthesia will be achieved with 2% lidocaine or 4% articaine containing 1:100,000 epinephrine and the tooth will be isolated under rubber dam.To minimize further bacterial contamination of the pulp, carious tissues will be progressively removed, starting at the periphery of the cavity and then over the pulp chamber roof.Once pulp chamber deroofing is complete, a fresh sterile bur will be used to remove all coronal pulp tissue to the level of the root canal orifices, under copious water irrigation. During this step, intra-operative assessment of pulp vitality will also be carried out. Healthy vital pulp will present as uniformly reddish pink vascular tissue, while non-vital necrotic pulp will present as dark avascular tissue with minimal bleeding or as yellowish liquefied areas. If pulp is judged to be necrotic, the tooth will be excluded from the study. Further treatment of such excluded teeth will be delivered following local management protocols.Haemostasis and disinfection of the radicular pulp tissue will be carried out by compressing a 5% NaOCl-soaked sterile cotton pellet over the pulp stumps for up to 8-min. Up to three attempts will be made to control pulp stump bleeding using moderate pressure applied with the NaOCl-dampened cotton pellet. Pulpal haemostasis will be assessed at three timepoints (3-, 6-, and 8-min) and the pulpotomy medicament placed over the pulp stumps as soon as haemostasis is achieved. If bleeding persists beyond 8-min, the radicular pulp shall be considered irreversibly inflamed, and the tooth will be excluded from the study. Further treatment of such excluded teeth will be delivered following local management protocols.Once haemostasis is achieved, 2 mm of a pre-mixed mineral trioxide aggregate (MTA) (NeoPutty, NuSmile, Houston, TX, U.S.A) medicament will be directly adapted over the pulp stumps ensuring that there is no porosity or any excess cement on the pulp chamber walls.The access cavity will be restored with a bulk-fill high-strength glass ionomer cement (3M ESPE Ketac Molar, Seefeld, Germany). Post-operative radiograph will be taken to confirm fidelity to the pulpotomy procedure.The pulpotomy-treated tooth will be prepared for receiving a full coverage stainless steel crown (SSC) one week after the pulpotomy procedure.

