### Target sample size

Sample size determination for this binary outcome non-inferiority randomised trial was calculated using a computer-generated system available online (https://www.sealedenvelope.com/power/binary-noninferior/). Based on previous clinical studies [29–31], a 95% success rate was assumed for both treatment interventions along with a 17% non-inferiority margin. Even an overall success rate of 78% for the experimental pulpotomy intervention would be considered non-inferior to the standard pulpectomy intervention. To obtain a power of 80% (β = 0.20) and a 2-sided α equal to 0.05, approximately 42 patients for both groups will be needed. To compensate for loss during follow-up and other causes of attrition, the targeted sample size will be 50 vital primary molar teeth diagnosed with irreversible pulpitis, distributed equally between the two trial treatment arms.

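### Intention to treat is the only analysis population named in a non-inferiority trial; a pre-specified per-protocol analysis should stand alongside it, although the likely inflation of error is modest

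*Protocol article*

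**What the plan says.** The Trial design section describes a "parallel, two-armed, open label, non-inferiority randomised controlled trial with a 1:1 allocation ratio". The Target sample size section sets the success rates and the margin: "a 95% success rate was assumed for both treatment interventions along with a 17% non-inferiority margin". It adds: "Even an overall success rate of 78% for the experimental pulpotomy intervention would be considered non-inferior".

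The only statement on who is analysed is in Statistical methods: "All analyses will use the ‘intention to treat’ principle". The article names no per-protocol set, as-treated set or sensitivity analysis by population.

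Four other places bear on how deviations could arise:

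- **Trial interventions.** The allocation is revealed during the operation, once vitality and haemostasis are confirmed. A post-operative radiograph checks fidelity to the procedure in both arms. The crown comes at a later visit: "The pulpotomy-treated tooth will be prepared for receiving a full coverage stainless steel crown (SSC) one week after the pulpotomy procedure". The pulpectomy arm has the same interval.
- **Follow-up timeline.** Outcomes are recorded at 6, 12 and 24 months.
- **Trial outcomes.** Success is judged from signs and symptoms and from the radiograph at recall. Re-treatment of the tooth is not among the listed criteria for failure.
- **Expected risks.** Children with continuing pain can obtain emergency care, and pulpotomy is described as the first stage of pulpectomy.

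**The concern.** In a superiority trial, analysis by randomised arm is cautious because deviations usually shrink the observed difference. In a non-inferiority trial a smaller observed difference is what the sponsor hopes to see, so the same shrinkage favours the claim. For that reason an analysis by randomised arm is normally read next to a per-protocol analysis.

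The mechanism that fits this trial is one-way. A pulpotomy tooth that stays painful could be re-treated, possibly with the comparator procedure, and be free of signs and symptoms at 24 months. Analysed as randomised under the stated success criteria, it could count as a pulpotomy success. If this happens to several of 25 teeth, the pulpotomy rate moves toward the pulpectomy rate for a reason unrelated to how well pulpotomy works. With intention to treat as the only population, the report would contain nothing to reveal this.

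**Working it through.** **Inputs from the article.** Success is 95% in both arms, the margin is 17 points, power is 80%, and alpha is 0.05 (called two-sided). About 42 patients are needed and 50 teeth are to be enrolled, 25 per arm. Treatment effects are to be given with 95% confidence intervals.

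**Assumed input.** The share *c* of pulpotomy teeth that take on the pulpectomy success rate but are analysed as randomised. The article gives no figure, so 0% to 20% is shown.

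**Step 1: the plan's own sample size.** With unpooled variance, n per arm = [2 × 0.95 × 0.05] × (z₁₋α + z₀.₈₀)² / 0.17².

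- One-sided alpha 0.05: 0.095 × (1.645 + 0.842)² / 0.0289 = 20.3, so 21 per arm and 42 in total. This reproduces the stated figure.
- One-sided alpha 0.025, which matches a 95% interval: 25.8, so 26 per arm and 52 in total. This does not reproduce it.

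The mismatch is a separate matter. It is noted here because the error rates below use the 95% interval that Statistical methods promises, that is, one-sided 0.025.

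**Step 2: shrinkage of the difference.** Put the truth exactly at the margin: pulpectomy 95%, pulpotomy 78%. The pulpotomy rate as analysed is 0.78(1 − c) + 0.95c, so the difference is 17(1 − c) points.

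- c = 10%: rate 79.7%, difference 15.3 points.
- c = 20%: rate 81.4%, difference 13.6 points.

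**Step 3: chance of a false claim at 25 per arm.** Non-inferiority is claimed if the lower 95% limit for pulpotomy minus pulpectomy lies above −17 points. The normal approximation is Φ[(0.17 − d)/SE − 1.96], where d is the difference as analysed. For c = 10%, SE = √(0.95 × 0.05/25 + 0.797 × 0.203/25) = 0.0915, and Φ(0.017/0.0915 − 1.96) = Φ(−1.774) = 3.8%. The exact column sums the binomial probabilities of all result pairs whose Newcombe limit clears the margin.

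| One-way crossover c | Difference analysed | Normal approximation | Exact, Newcombe |
|---|---|---|---|
| 0% | 17.0 | 2.5% | 2.2% |
| 10% | 15.3 | 3.8% | 3.2% |
| 20% | 13.6 | 5.7% | 4.7% |

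If the same shares crossed over in both arms, the exact figures would be 4.9% and 9.6%. The conduct of this trial makes that hard to believe (see the objection).

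**Step 4: precision of a per-protocol set.** Suppose 21 teeth per arm remain and true success is 95% in both arms. Power at one-sided 0.025 is then 71% by normal approximation, against 79% with 25 per arm. With exact Newcombe limits the figures are 46% and 57%.

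**The case against.** The strongest defence is that the usual source of dilution is largely closed by design. Necrotic teeth and teeth with uncontrolled bleeding are excluded before allocation. The allocated procedure follows at once, and a radiograph confirms it. This stands, and it is why two-way crossover of 10% to 20% is not a realistic case.

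A missed crown is also not a crossover. Such a tooth has still had its allocated pulp treatment and a glass ionomer restoration, and if the missing crown harms both arms alike the difference need not shrink. Parents unwilling to have crowns are excluded in any case. This too stands.

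A reader might take the gap between 42 and 50, which is 16%, as the share of off-protocol teeth. The article does not support that. It is an allowance for loss to follow-up and other attrition, and a tooth with no outcome raises a missing-data question, not one of dilution.

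A reader might also infer that intention to treat is the wrong primary analysis here, or that a false claim is likely. Neither follows. Analysis by randomised arm keeps the protection of randomisation, whereas a per-protocol set is open to selection bias. Dilution is the usual direction but not a certain one: a deviation that harms only one arm could act the other way.

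Last, it can be said that supplementary analysis sets belong in an analysis plan that is not shown. That would answer silence. But the sentence speaks of all analyses, so a later plan that added a per-protocol set would depart from the published text. This part of the defence only softens the point.

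**Conclusion.** The point holds in a limited form. The article fixes one analysis population for a non-inferiority trial, and in that population some deviations, later re-treatment of painful pulpotomy teeth above all, can favour the claim unseen. Under assumed one-way crossover of 10% to 20%, with the true difference at the 17-point margin and 25 teeth per arm, the false non-inferiority rate rises from about 2.2% to between 3.2% and 4.7%. That is roughly 1.5 to 2 times the rate without crossover, and still below 5%. The result rests on three assumptions: the crossover share, for which the article gives no figure; that crossing teeth take on the full pulpectomy success rate; and that the decision uses the 95% interval. The trial should make the change, but the point does not undermine the design.

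**What to change.** Replace the sentence on intention to treat with wording such as:

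> The primary analysis is by randomised arm. A pre-specified per-protocol analysis (allocated procedure completed and no major deviation, with failures before the crown visit kept as failures) is reported alongside against the same 17-point margin. A non-inferiority conclusion is described as robust only if the two analyses agree.

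The list of major deviations should be fixed before outcomes are seen. It should say how a re-treated tooth is counted in each analysis, because simply dropping such teeth from the per-protocol set could itself remove pulpotomy failures. Placement of a crown should not be a condition of entry, since that would discard teeth that fail in the first week.

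Two stricter rules are not advised. Making success in both sets a formal condition is debatable with about 21 to 25 teeth per arm. Counting only missing pulpotomy outcomes as failures is close to unpassable: with 4 of 25 missing per arm and 95% true success in both arms, the margin would be met about 0.1% of the time.

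The cost is one amended sentence and one more analysis of data already collected. The downsides are a smaller, less precise set that is open to selection bias, and a claim that is somewhat harder to call robust.

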### Objectives

Compare the treatment effectiveness of full pulpotomy vs. single-visit pulpectomy in the management of vital primary molars diagnosed with symptomatic irreversible pulpitis based on the clinical and radiographic outcomes of the treated teeth over a two-year period.Assess influence of baseline pre-operative variables (age; gender; tooth type; site of caries; pre-operative furcal radiolucency; pre-operative pain intensity) and intra-operative factors (time taken to achieve haemostasis) on treatment outcomes.

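### The 17-point risk-difference margin is never tested: the only treatment comparison stated is adjusted logistic regression, with no link to the margin and about an even chance of no finite odds ratio at the planned success rate

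*Protocol article*

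**What the plan says.** Trial design describes a "non-inferiority randomised controlled trial with a 1:1 allocation ratio". Under Target sample size, "a 95% success rate was assumed for both treatment interventions along with a 17% non-inferiority margin", and the scale of the margin is settled by the next sentence: "Even an overall success rate of 78% for the experimental pulpotomy intervention would be considered non-inferior to the standard pulpectomy intervention". Since 95 - 17 = 78, the margin is a difference in success proportions. The size follows from it: "To obtain a power of 80% (β = 0.20) and a 2-sided α equal to 0.05, approximately 42 patients for both groups will be needed", raised for attrition so that "the targeted sample size will be 50 vital primary molar teeth diagnosed with irreversible pulpitis, distributed equally between the two trial treatment arms".

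Statistical methods names one method for comparing treatments: "Binary logistic regression models will be applied to analyse all outcome measures stated in the protocol adjusting for covariates thought to be of prognostic importance". The primary outcomes, clinical and radiographic success, are among those outcome measures. The section adds two-sided p-values at 0.05 and says that "the treatment effect estimates will be presented with 95% confidence intervals". It does not name the scale of the effect, and it does not mention the margin. The parametric or non-parametric tests also listed there relate outcomes to baseline variables, not to the margin.

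**The concern.** A non-inferiority trial is decided by setting a confidence limit for the treatment effect against the margin, on the margin's own scale. Here the margin and sample size are on the risk-difference scale, while the stated model works on the log-odds scale. Its usual two-sided p-value tests an odds ratio of 1, which is a question of difference and not of non-inferiority. Followed as written, the analysis never tests the 17 points.

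The second problem is sparse data. With success assumed at 95%, an arm of 21 or 25 teeth may well have no failures, and ordinary maximum-likelihood logistic regression then gives no finite treatment coefficient. At stake is whether the trial can state a result on its own question, and whether the scale or a rescue method ends up being chosen after the data are seen.

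**Working it through.** **Inputs.** From Target sample size: success 95% in both arms, margin 17 points, 42 teeth in total before attrition (21 per arm), 50 after (25 per arm). From Background/rationale: 88% pulpectomy success in the cited retrospective study, used below as an alternative control rate. Success of 90% is a sensitivity value assumed here.

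**1. The plan's own figure.** The usual risk-difference formula is n per arm = 2 × 0.95 × 0.05 × (z_α + z_β)² / 0.17².
- One-sided α 0.05: n = 20.3, so 21 per arm and 42 in total. This matches.
- One-sided α 0.025 (the two-sided 0.05 in the text): n = 25.8, so 26 per arm and 52 in total. This does not match.

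The stated 42 therefore comes from a risk-difference calculation. Its one-sided 5% level is a separate sample-size matter, but it bears on the cost of the fix.

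**2. The margin as an odds ratio.** OR = [p_E/(1 - p_E)] / [p_C/(1 - p_C)] with p_E = p_C - 0.17.

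| Control success | Success at the margin | Odds ratio |
|---|---|---|
| 95% | 78% | (0.78/0.22)/(0.95/0.05) = 0.187 |
| 90% | 73% | (0.73/0.27)/(0.90/0.10) = 0.300 |
| 88% | 71% | (0.71/0.29)/(0.88/0.12) = 0.334 |

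Conversely, if 0.187 were fixed as the margin and control success were 90%, the experimental odds at the margin would be 0.187 × 9 = 1.68, or 62.7% success. That tolerates a loss of 27.3 points.

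**3. Expected failures.** 42 × 0.05 = 2.1; 50 × 0.05 = 2.5.

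**4. No finite treatment estimate.** This happens when at least one arm has no failures: P = 1 - (1 - p^n)².

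| True success | 25 per arm | 21 per arm |
|---|---|---|
| 95% | 0.95^25 = 0.277, P = 47.8% | 0.95^21 = 0.341, P = 56.5% |
| 90% | 0.90^25 = 0.072, P = 13.8% | 0.90^21 = 0.109, P = 20.7% |

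These figures are for the treatment coefficient alone. Covariates add ways to fail. In a simulation of 2000 trials at 95% success with three covariates unrelated to outcome (one continuous, two evenly split binary; an assumption, since the article fixes no list), some coefficient was non-estimable in about 69% of trials with 25 per arm and 75% with 21.

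**5. Can the choice change the conclusion?** Two plausible results with 25 per arm:
- 25/25 v 25/25: the Wilson lower limit for one arm is 25/(25 + 1.96²) = 0.867, so the Newcombe 95% lower limit for the difference is -13.3 points and non-inferiority is shown. Logistic regression gives no estimate.
- 24/25 v 24/25: the Newcombe lower limit is -15.9 points, so non-inferiority is shown. The unadjusted odds ratio is 1 with standard error √[2(1 + 1/24)] = 1.443 on the log scale. The Wald lower limit is exp(-1.96 × 1.443) = 0.059, below 0.187, so non-inferiority is not shown.

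**6. Exact chance of showing non-inferiority** at true 95% in both arms, summed over all binomial results, two-sided 95% intervals:

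| Method | 25 per arm | 21 per arm |
|---|---|---|
| Newcombe interval against -17 points | 57% | 46% |
| Miettinen-Nurminen interval against -17 points | 57% | 45% |
| Unadjusted logistic Wald interval against OR 0.187, non-estimable counted as not shown | 8% | 5% |

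**The case against.** **The odds ratio can be brought to the margin.** A logistic model can give a risk difference by marginal standardisation, or the margin can be converted at the planned control rate to 0.187. It would be too strong to say that the model's result can never be read against 17 points. But the article states neither route. Conversion depends on a control rate that the trial itself will estimate, and standardising an ordinary maximum-likelihood fit does not cure separation.

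**A statistical analysis plan may settle it.** It may add the detail. But the article has already named a model for all outcome measures that does not address its margin, so this is a choice badly fixed rather than a detail left out.

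**Half of trials would have an unusable interval.** A reader might infer this from the 48% to 57%. Those figures describe a non-finite point estimate. The interval is lost at that rate only with Wald limits, which the article does not specify. Non-inferiority needs only the lower limit. If only the pulpotomy arm has no failures (0.277 × 0.723 = 20% with 25 per arm; 0.341 × 0.659 = 22% with 21), a likelihood-based lower limit is still finite. That limit is lost when the pulpectomy arm has no failures: 28% or 34%. This part of the objection stands.

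**An overloaded seven-factor model.** The objective to "Assess influence of baseline pre-operative variables (age; gender; tooth type; site of caries; pre-operative furcal radiolucency; pre-operative pain intensity" and haemostasis time invites the inference that all seven factors enter one confirmatory model with far too few events. The documents do not support it. The covariates for adjustment are neither listed nor counted, the influence of baseline variables is assigned to separate tests, and nothing is called confirmatory. Tests of one variable at a time would have little power here, but they do not fail through separation.

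**True success may be lower.** At 90% the estimability problem shrinks to 14% to 21%. The mismatch of scale remains at any rate.

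**Conclusion.** The point holds. The margin is an absolute 17 points, and the only stated treatment comparison neither produces that quantity directly nor is linked to it. This rests on the text alone, whatever the true success rate. The article does not use the words primary analysis for the logistic model; the point follows because the model is assigned to every outcome measure.

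The estimability figure, 48% (25 per arm) to 57% (21 per arm), rests on the article's own 95% success in both arms, independent teeth and ordinary maximum likelihood. It concerns the point estimate of the treatment odds ratio; standard Wald intervals fail with it. Adjustment makes estimation more fragile, by an amount that cannot be fixed without a covariate list. The matter should be corrected before outcome data are analysed.

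**What to change.** State the primary non-inferiority analysis as the unadjusted difference in success proportions, pulpotomy minus pulpectomy, with a two-sided 95% score-type interval (Newcombe or Miettinen-Nurminen). Conclude non-inferiority if the lower limit is above -17 points. This gives an estimate and interval for every possible result, including no failures in either arm.

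Keep adjusted logistic models as supportive, with few covariates named in advance and a method that tolerates sparse events. Firth penalisation is one option; the documents do not make it the only one.

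The change to the analysis is one of wording, but it is not free. With this interval, the exact chance of showing non-inferiority at true 95% in both arms is about 57% with 25 per arm and 46% with 21. The 80% in Target sample size must therefore be restated for the interval actually used. The fix does not create this shortfall. It makes visible that 42 teeth reproduces only at a one-sided 5% level under a normal approximation.

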**Methods/design:**

This clinical study is a parallel, two-armed, open label, non-inferiority RCT with a 1:1 allocation ratio between the experimental intervention arm (pulpotomy) and the active comparator arm (pulpectomy). Healthy cooperative children, between 4–9 years of age, who have painful primary molars with clinical symptoms typical of irreversible pulpitis will be recruited after obtaining informed consent from their parents/legal guardians. 50 vital primary molars clinically diagnosed with symptomatic irreversible pulpitis will be randomly distributed between the two treatment arms. The primary outcomes that will be assessed are clinical and radiographic success after six-months, one-year and two-years of the trial interventions. The influence of baseline pre-operative variables (age; gender; tooth type; site of caries; pre-operative furcal radiolucency; pre-operative pain intensity) and intra-operative factors (time taken to achieve haemostasis) on treatment outcomes will also be assessed. The secondary outcome evaluated will be the immediate (24 h and 7 d) post-operative pain relief afforded by the two treatment interventions.

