#### Secondary outcomes

*Immediate post-treatment pain relief:* post-operative pain felt by the child in the immediate aftermath of the trial interventions will recorded at two time-points (24 h and 7 d) using the VAS. The pain scores recorded will be used to evaluate pain reduction afforded by the two trial interventions.

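### Binary logistic regression is fixed for all outcomes, but the only secondary outcome is a five-level pain score with no binary definition

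*Protocol article*

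**What the plan says.** Statistical methods names one model type and gives its scope: "Binary logistic regression models will be applied to analyse all outcome measures stated in the protocol", with adjustment for prognostic covariates.

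Pain is one of those outcome measures, and it is the only secondary one. The abstract says: "The secondary outcome evaluated will be the immediate (24 h and 7 d) post-operative pain relief afforded by the two treatment interventions". The Secondary outcomes section adds: "The pain scores recorded will be used to evaluate pain reduction afforded by the two trial interventions".

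Trial interventions describes the instrument as a "validated five-face visual analogue scale (VAS) commonly used for pain intensity measurement in children", from which the child picks one face before treatment. The same scale is used at 24 h and 7 d. No section gives a cut-off, a responder definition or a pain-free rule.

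A further sentence in Statistical methods reads: "Appropriate parametric or non-parametric tests will be used to determine any significant relationship between treatment outcomes and variables in the study". The variables it then lists are age, gender, tooth or caries type, and pre-operative furcal rarefaction and pain intensity. Treatment arm is not among them.

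**The concern.** A binary logistic model needs a two-valued response, and the pain outcome has five ordered values. To follow the stated method, an analyst must first collapse the score, and the protocol does not say where.

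Two things are at stake. The first is precision: at 25 teeth per arm there is little to spare, and one cut of a five-level score can discard information. The second is freedom of choice. Five levels allow four cuts, and with two time-points that makes 4 × 2 = 8 possible binary results, before any cut on change from baseline is counted. Early pain matters to the trial's message, because the Discussion puts forward less pain and discomfort as a potential benefit of the more conservative approach.

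**Working it through.** **The plan's own figure.** The protocol gives no calculation for pain. Its only sample-size figure, 42 in total, concerns binary success: "a 95% success rate was assumed for both treatment interventions along with a 17% non-inferiority margin". With n per arm = (z₁₋α + z₀.₈₀)² × 2 × 0.95 × 0.05 / 0.17², a one-sided α of 0.05 gives (1.645 + 0.842)² × 0.095 / 0.0289 = 20.3, so 21 per arm and 42 in total. A one-sided α of 0.025 gives 26 per arm, or 52. The stated 42 therefore reproduces at one-sided 0.05, although the text calls α two-sided. That is a separate matter and has no bearing on pain.

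**Inputs for pain.** From the protocol: five ordered categories, 25 teeth per arm (50 divided equally), and no cut. Assumed, because the protocol is silent: the share of children choosing each face, and an odds ratio of 4 for the power simulation.

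**Formula.** Under proportional odds, the information on the log odds ratio from a score with category shares p₁…p₅ (arms pooled) is proportional to (1 − Σpₖ³)/3. A single cut with share q below it gives q(1 − q). The share of information kept is q(1 − q) ÷ [(1 − Σpₖ³)/3].

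**Worked example, even use (20% each).** Σp³ = 5 × 0.008 = 0.04, so the full score gives 0.96/3 = 0.32. A 20/80 cut gives 0.16, and 0.16/0.32 = 50%. A 40/60 cut gives 0.24, and 0.24/0.32 = 75%.

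**Worked example, strong floor (70/15/8/5/2%).** Σp³ = 0.347, so the full score gives 0.653/3 = 0.2177. None versus any gives 0.7 × 0.3 = 0.21, and 0.21/0.2177 = 96.5%. The highest cut gives 0.98 × 0.02 = 0.0196, and 0.0196/0.2177 = 9%.

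Information kept, by cut (1\|2 means lowest face versus the rest):

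| Assumed shares (%) | 1\|2 | 2\|3 | 3\|4 | 4\|5 |
|---|---|---|---|---|
| Even, 20 each | 50% | 75% | 75% | 50% |
| Mid-peaked, 10/20/40/20/10 | 29% | 69% | 69% | 29% |
| Low-skewed, 40/30/15/10/5 | 80% | 70% | 42% | 16% |
| More skewed, 60/20/10/5/5 | 93% | 62% | 35% | 18% |
| Strong floor, 70/15/8/5/2 | 96.5% | 59% | 30% | 9% |

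**Power check by simulation.** Settings: 25 per arm, odds ratio 4, 4,000 runs, two-sided 5%, no covariates. The shares apply to the reference arm. Wilcoxon is compared with a two-proportion test at each cut:

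| Shares | Wilcoxon | 1\|2 | 2\|3 | 3\|4 | 4\|5 |
|---|---|---|---|---|---|
| Even | 75% | 63% | 68% | 56% | 33% |
| Mid-peaked | 75% | 48% | 70% | 46% | 13% |
| Low-skewed | 70% | 71% | 45% | 25% | 2% |
| Strong floor | 44% | 46% | 25% | 6% | 0.1% |

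In the last two rows the none-versus-any cut costs no power. In every row a badly placed cut costs a great deal.

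**The case against.** **The analysis plan may define the cut.** A responder definition for a secondary outcome is often left to that document, and its absence from an article is not a fault. This stands in part: one cannot conclude that the cut will be chosen after the data are seen. But the article is not silent. It names a model and extends it to every outcome. An analysis plan that follows it has to dichotomise, and one that uses an ordinal or rank method departs from it.

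**Non-parametric tests are already allowed.** The sentence that allows them concerns relations between outcomes and listed baseline variables, not the comparison of arms.

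**The loss is unproven.** A reader might infer that dichotomising wastes much of the information in this trial. The protocol does not support that as a fact. It gives no score distribution, and the best-placed cut loses only 3.5% to 31% in the cases above. The efficiency formula also rests on proportional odds, which is the assumption behind the recommended model.

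**Reduction can still be measured.** A reader might also infer that a binary analysis could not address pain reduction. That is not so. A fall of a set number of faces is a binary endpoint, and a pain-free endpoint can be adjusted for the pre-operative score, which is collected. Either one needs a stated threshold.

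**Conclusion.** The mismatch holds: the method fixed for all outcomes does not fit the five-level pain score as the protocol describes it. Its cost depends on two things the protocol does not give, the distribution of scores and the cut. Under proportional odds and the assumed distributions, the loss is 25% to 50% with even use of the faces. It is near nil (3.5%) for none versus any under a strong floor, and 84% to 91% for the worst cut of the low-skewed and strong-floor scores.

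The consequence is confined to the secondary outcome. Clinical and radiographic success are binary and suit the model type, and the sample size does not rest on pain. It would be wrong to read this point as casting doubt on the non-inferiority comparison.

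**What to change.** Restrict binary logistic regression to clinical and radiographic success, and add a sentence such as: *Pain scores at 24 h and at 7 d will each be compared between arms by a proportional-odds model with treatment and pre-operative pain score as covariates, reporting the common odds ratio with its 95% confidence interval; a Wilcoxon rank-sum test will serve as a check.* The rank test is useful because cells may be sparse at 25 teeth per arm, which makes the proportional-odds assumption hard to verify.

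If a binary pain endpoint is preferred, that also cures the defect, provided its cut and the reason for it are written down before the data are seen.

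The cost is one sentence. The pre-operative, 24 h and 7 d scores are already collected, the named software offers ordinal regression, and neither sample size nor conduct changes.
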